### Objective

2.5

#### Primary objective

2.5.1

The primary objective is to examine yogurt-dependent bacterial (YDB) DNA counts in fecal and blood samples before and after dairy consumption. YDB, such as *Lactococcus lactis*, are transient residents of the human gut, only present following dairy intake, and therefore represent modifiable components of the intestinal microbiome. Detection of YDB DNA fragments in the bloodstream after dairy reintroduction will provide definitive evidence on the extent to which the blood microbiome reflects relevant changes in the intestinal microbiome. In this specific study, the use of a commercial yoghurt (but verified by independent agar growth testing) containing a defined consortium of bacteria adds signature species whose detection provides convincing signals in this respect.

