### Study design

2.1

We will perform a within-subjects crossover trial with a single arm to study the effect of yogurt on the blood and fecal YDB levels in healthy volunteers. Participants will first undergo a 10-day period of dairy product withdrawal. Given that the half-life of bacterial DNA in blood is likely less than 24 h, a 10-day withdrawal period should be sufficient to substantially reduce circulating DNA fragments originating from *L. lactis*. Following the reintroduction of dairy (via yogurt consumption that is host to LGG, LA-5 and BB-12 cultures), we expect these specific bacteria and other YDB DNA to reappear in the bloodstream. While the precise kinetics of this reappearance are not yet known, our study is designed to detect these temporal changes and establish a foundation for understanding the dynamic relationship between dietary intake, the gut microbiome, and the blood microbiome.

This study is approved by the ethics committee of Erasmus Medical University Center Rotterdam in May 2025 (NL88008.078.24) and is registered at www.clinicaltrials.gov (NCT06944002), hence prior to participant's enrollment. This study will be conducted in accordance with the principles of the Declaration of Helsinki (75th WMA General Assembly, Helsinki, Finland, October 2024) and the Medical Research Involving Human Subjects Act (WMO). Interested volunteers will be provided with detailed information about the study and will give written informed consent prior to participation.

Participants will be studied at multiple time points using a within-subject crossover design (Fig. 1). At baseline, prior to any dietary intervention, blood and stool samples will be collected. Following this, participants will abstain from all dairy products for 10 days, after which a second set of blood and stool samples will be collected to confirm the expected disappearance of YDB DNA from both fecal and circulating microbial DNA pools.

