**Fig. 1 fig1:**
[figure not shown]
Study design. In this within-person crossover trial, the volunteers will be studied multiple times: a baseline sample of blood and stool will be collected before the withdrawal of any dairy product. Ten days later, the same samples will be collected again to verify if milk and/or yogurt-associated bacteria disappear from the stool and the blood DNA. Subsequently, volunteers will be instructed to drink minimal 700 mL yogurt during breakfast for 7 consecutive days. Three time points will be chosen to capture the dynamics of yogurt-associated DNA gut-to-blood translocation: 24 h, 48 h, and one week after the reintroduction of dairy products. Participants will be invited to visit the hospital for a total of five times. The dairy products used in this study will be provided by the investigational team.

Subsequently, participants will reintroduce dairy into their diet by consuming 700 mL of yogurt daily for seven consecutive days, an amount consistent with recommendations from the United States Dietary Guidelines [18]. Given the current lack of data on the kinetics of bacterial DNA translocation from the gut to the bloodstream, we will collect post-intervention blood and stool samples at three distinct time points: 24 h, 48 h, and one week following the reintroduction of dairy. During this reintroduction phase, participants will also be permitted to consume other dairy products in addition to yogurt.

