### Power analysis

2.6

This is a pilot study. This research has never been conducted before, making it difficult to determine a definite sample size. Based on published studies showing significant change in the relative abundance of gut microbiome at the phylum level upon consumption of fermented milk in 6 volunteers (Firmicutes and Bacteroidetes; p < 0.05 when comparing milk consumption vs. baseline) [20], and that the relative abundance of Bifidobacterium species increased following the consumption of human milk oligosaccharides by 7 volunteers over 7 days (p < 0.05 when comparing four type of milk concentrations with baseline) [21], we have chosen to include 10 volunteers for this study. If this is not sufficient to convincingly demonstrate trends of *Lactococcus lactis* DNA during 7 days of milk consumption intervention, then blood microbiome studies may not be powerful enough to show meaningful changes in intestinal microbiome composition.

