Because the blood microbiome may be less than 5 % of the entire blood DNA, interpretation of such low microbial biomass is challenged by potential environment contamination (e.g., lab equipment and kitome) [22,23]. In addition, the definition of a core blood microbiome is further complicated by that the assembled genomes of many bacteria (especially older assemblies) are contaminated by human DNA sequences, leading to false-positive results. The latter issue is considered the biggest problem in the analysis and interpretation of blood microbiomes [14]. The current study, because of its longitudinal character and its reliance on the introduction of defined species with relatively novel assemblies in the database, is designed to provide of proof-of-principle on whether these problems can be overcome. Further, additional power will be added to the current study by introduction of additional controls: we will include a series of reference controls designed to account for all potential sources of contamination and misinterpretation described above (Fig. 3).2DNA extraction and shotgun sequencing

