### Statistical analysis

2.9

The primary outcome is the change in relative abundance of blood YDB DNA across five time points. This will be analyzed using repeated measures ANOVA to detect statistically significant within-subject changes over time. The secondary outcomes include changes in all other non-human microbial DNA, which will also be analyzed using repeated measures ANOVA. All statistical tests will be two-tailed, with significance set at p < 0.05.

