## Discussion

3

The existence of a common core blood microbiome in humans remains a subject of debate [10,13]. Most previous studies are cross-sectional and often lack rigorous controls for environmental contamination and database misclassification, which poses a significant challenge and hinders progress in the field. Another major limitation is the absence of longitudinal within-subject controls, which are essential for identifying and correcting potential false positives or negatives caused by individual variability and limitations in bioinformatics pipelines [14]. Furthermore, while the gut microbiome is frequently proposed as the primary source of blood microbial DNA, this hypothesis has not yet been definitively proven.

To overcome these challenges, a longitudinal design using a safe, well-characterized intervention that reliably alters the gut microbiome offers a promising solution. Yogurt, generally regarded as safe and nutritional beneficial, increase levels of beneficial bacteria such as *Lactococcus* and *Lactobacillus*, which are closely linked to immune function [40]. Given the established translocation of gut microbiome-derived metabolites, it is plausible that microbial DNA from yogurt-sensitive gut bacteria could also enter circulation and contribute to the composition of the core blood microbiome. In addition to its microbiome-modulating effects, yogurt provides essential vitamins and minerals such as riboflavin, zinc, selenium, and magnesium that support immune health as well. These combined advantages make yogurt a suitable, targeted and practical modulator for studying the presence and behavior of YDB DNA in circulation.

If cmDNA in blood correlates with the fecal microbiome, the use of defined probiotic strains in yogurt as spike-in controls may offer evidence supporting cm DNA as a valid representation of the colonic microbial composition of the participants involved. Importantly, while these introduced species primarily serve as a proof-of-principle to demonstrate detectability in blood, comprehensive microbiome profiling of fecal material will allow direct correlation analyses with respect to the amount of these bacteria in the volunteer intestine. Thus substantial insight into the relationship between gut and blood microbial signals is expected to be gained in this respect. Should proof-of-principle be established, a future dose response study will allow making more precise quantification and validation of these correlations.

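### Section 2.5.1 calls detection of yogurt-dependent bacterial DNA in post-yogurt blood definitive, without requiring a rise over the post-withdrawal (D0) sample or a signal above the reference controls

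*Protocol article*

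**What the plan says.** All references are to the protocol article.

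- **2.5.1 Primary objective** opens with a comparison: "The primary objective is to examine yogurt-dependent bacterial (YDB) DNA counts in fecal and blood samples before and after dairy consumption". It then states what the result will mean: "Detection of YDB DNA fragments in the bloodstream after dairy reintroduction will provide definitive evidence". The closing sentence of the section likewise treats detection of the yogurt's signature species as convincing. Neither sentence mentions the D0 sample, a control, a read limit or a number of participants.
- **2.1 Study design** gives the D0 sample, taken after 10 days without dairy, a purpose: "to confirm the expected disappearance of YDB DNA from both fecal and circulating microbial DNA pools". Blood is then drawn at "three distinct time points: 24 h, 48 h, and one week following the reintroduction of dairy".
- **2.8.1** plans a yogurt-DNA spike-in on pre-intervention blood, a commercial microbial standard and, in Fig. 3, unspiked reference controls (placenta blood as the negative control, virus-positive blood, organoids, pig and rat blood). On bacterial assemblies that contain human sequence and so yield false positives, it says: "The latter issue is considered the biggest problem in the analysis and interpretation of blood microbiomes".
- **2.9 Statistical analysis** fixes the primary outcome: "The primary outcome is the change in relative abundance of blood YDB DNA across five time points". The test is a repeated measures ANOVA, two-sided at 0.05.
- **3 Discussion** says that "these introduced species primarily serve as a proof-of-principle to demonstrate detectability in blood", in a sentence that goes on to correlation with fecal amounts.

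**The concern.** In a low-biomass matrix where false assignment is expected, a post-yogurt read is evidence of translocation only if it was absent or lower before yogurt and exceeds what the same pipeline reports in material that should contain none. The design collects what is needed for both comparisons. The sentence that says what the trial will prove asks for neither.

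The study is presented as one that will establish or rule out circulating microbial DNA as a representative of the gut microbiome. If the written standard is detection, a report could cite 2.5.1 to claim proof from a few background reads, even if the same reads occurred at D0 or the ANOVA showed no change.

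**Working it through.** **The plan's own figure.** The only design number is the sample size: "we have chosen to include 10 volunteers for this study". Section 2.6 reaches it by analogy with two studies of 6 and 7 volunteers. It gives no effect size, SD, power or false-positive rate, so there is nothing to reproduce.

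**Side by side.** The opening of 2.5.1 is about before versus after, 2.1 uses D0 to confirm disappearance, 2.9 tests change, and 2.8.1 supplies controls for background. The interpretive sentence in 2.5.1 rests on detection after yogurt. No part of the article turns D0 or the controls into a condition for calling a post-yogurt signal real.

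**Illustration of what detection alone could be worth.** Inputs: 10 participants (2.6) and 3 post-yogurt samples each (2.1), so 10 × 3 = 30 samples. The background false-call rate p per sample is not in the document and is assumed. With independent errors and no true effect,

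P(at least one false detection) = 1 − (1 − p)^30.

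| assumed p | one or more false calls in 30 | same, with the participant also negative at D0 |
|---|---|---|
| 0.5% | 14.0% | 13.9% |
| 1% | 26.0% | 25.8% |
| 2% | 45.5% | 44.8% |
| 3% | 59.9% | 58.7% |
| 5% | 78.5% | 76.7% |
| 10% | 95.8% | 93.9% |

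The last column is 1 − [1 − (1 − p)(1 − (1 − p)^3)]^10. At p = 5%: 1 − 0.95^3 = 0.1426; × 0.95 = 0.1355; 1 − 0.8645^10 = 76.7%. Merely adding a D0-negative condition therefore barely helps. What is needed is a test of change.

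The middle column passes 50% at p = 1 − 0.5^(1/30) = 2.28%. Holding it to 5% would need p = 1 − 0.95^(1/30) = 0.17%. If four taxa (L. lactis, LGG, LA-5, BB-12) each had an independent 1% error, the figure would be 1 − 0.99^120 = 70%.

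**Sensitivity to independence.** With errors clustered by visit or by participant (beta-binomial, correlation 0.1 to 0.3), p = 3% gives 32% to 56% instead of 60%, and p = 5% gives 48% to 75% instead of 79%.

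**The planned test under the same null.** In 10,000 simulated trials per setting (10 people × 5 visits, sporadic lognormal false positives), the repeated measures ANOVA rejected in 0.04% (p = 1%), 0.3% (3%), 0.7% (5%) and 1.6% (10%). Testing change thus guards against this kind of sporadic background. The omnibus F test, however, does not say which visits differ or in which direction. A fall from baseline to D0 alone could make it significant.

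**A supportive paired test.** For an exact McNemar test of positivity at D7 against D0 with n = 10, six one-way conversions with none in reverse give 2 × 0.5^6 = 0.031, and five give 0.0625. With equal, independent positivity of 2% to 50% at both visits, two-sided rejection is at most 0.9%. With 5% positive at D0, power is 27%, 71%, 88% and 97% for D7 positivity of 50%, 70%, 80% and 90%.

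**The case against.** The tempting stronger reading is that the trial has a success rule under which one YDB fragment in any of 30 post-yogurt samples counts as proof, and that this rule succeeds in most null trials. The document does not support it:

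- Section 2.5.1 does not say any detection or set a success criterion. It speaks of the extent to which blood reflects the gut, and it opens with a before-and-after objective.
- D0 and the controls are part of the plan: D0 is meant to confirm disappearance, the ANOVA includes D0, and 2.8.1 describes the controls at length. It also says that the longitudinal design and defined species with newer assemblies are meant to test whether the false-positive problem can be overcome.
- Section 2.8.2 drops short fragments and genes with two or fewer mapped reads, so a single stray read would not make a call.
- The independence model fits poorly. Misassigned host reads would tend to recur at every visit, D0 included, and reagent contamination would cluster by batch. Every p is assumed, and at 1% to 2% fewer than half of null trials show a false call.
- The Discussion is hedged: it makes the inference conditional on correlation with the fecal microbiome.

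All of this stands against the stronger reading. It does not rescue the sentence itself. A recurrent host-read background is exactly the case in which detection after yogurt proves nothing and only comparison with D0 would reveal it. A numerical limit may fairly be left to a fuller document. The complaint here is that the article says outright what will count as definitive, and by its own account of false positives that statement is too strong.

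**Conclusion.** The point holds as an overstated and mismatched evidential claim in 2.5.1. Detection alone is called definitive, although section 2.8.1 explains why it cannot be, and although 2.9 and the planned controls offer a better standard. This conclusion comes from the text and needs no assumed rate.

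Its numerical size is illustrative only: 26% to 96% for assumed independent error rates of 1% to 10% per sample, lower under clustering, and above one half only from about 2.3%. These are not error rates of the trial's primary analysis, whose simulated null rejection was at most 1.6% for the same assumed rates. The sponsor should correct the wording, because that sentence carries the main conclusion.

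**What to change.** Reword 2.5.1 and remove the word definitive for detection alone. Claim proof-of-principle only if both conditions hold:

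1. The signature taxa (LGG, LA-5, BB-12, L. lactis) in blood rise significantly within person from D0 to after reintroduction, tested as a directed contrast within the 2.9 analysis.
2. The post-reintroduction signal exceeds a background limit fixed in advance from the unspiked negative controls.

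An exact McNemar test of positivity at D7 versus D0 can be added as support. It should not be the sole criterion, because it drops the 24 h and 48 h samples and the abundance outcome and has little power if only about half of participants convert.

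Cost: a change of wording, one prespecified contrast and one limit from controls already planned. No new samples are needed. The claim becomes somewhat harder to make.

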**Conclusion:**

This pilot study will test whether blood-derived microbial DNA can serve as a valid surrogate for gut microbiome composition. If successful, this approach may provide a more stable and integrative alternative to fecal sampling and support future biomarker development and mechanistic research.

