#### Intervention visit

2.7.4

Participants will attend three additional morning visits during the intervention phase: Day 12 (24 h after reintroducing yogurt); Day 13 (48 h after reintroduction) and Day 18 (after 7 days of yogurt consumption). At each time point, participants will provide the same clinical and biological data as collected during the baseline visit. No follow-up visits are scheduled beyond this point.

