#### DNA extraction and shotgun sequencing

2.8.1

1Pipeline and experimental controls

As the central aim of this study is detect yogurt-derived bacterial DNA in blood, we will include an in-vitro control to validate the sensitivity and specificity of our detection pipeline. Blood sample collected at pre-intervention visit, following a 10-day withdrawal from yogurt and all other diary products, will be used for this purpose. Specifically, defined quantities of yogurt DNA will be spiked into participant blood samples prior to DNA extraction. This setup will allow us to confirm that our pipeline can reliably detect yogurt-derived bacterial DNA within a blood matrix (Fig. 3).

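### Dairy-bacterial DNA in blood after yogurt cannot give the definitive evidence that section 2.5.1 claims, because no feature of the design separates absorbed food DNA from DNA released by bacteria in the gut

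*Protocol article*

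**What the plan says.** Section 2.5.1 makes YDB DNA counts in stool and blood the primary objective and says that finding YDB DNA in blood after reintroduction "will provide definitive evidence on the extent to which the blood microbiome reflects relevant changes in the intestinal microbiome". The Abstract's conclusion sets the wider aim: "This pilot study will test whether blood-derived microbial DNA can serve as a valid surrogate for gut microbiome composition".

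Section 2.9 defines the primary outcome as the change in relative abundance of blood YDB DNA over five time points, tested by repeated measures ANOVA. It contains no term that links blood to stool.

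On design, section 2.1 states "We will perform a within-subjects crossover trial with a single arm", with participants "consuming 700 mL of yogurt daily for seven consecutive days". During that week "participants will also be permitted to consume other dairy products in addition to yogurt". Section 2.7.4 ends sampling at the day-18 visit: "No follow-up visits are scheduled beyond this point". Section 2.8.1 describes the target as DNA from the product: "As the central aim of this study is detect yogurt-derived bacterial DNA in blood".

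The Discussion is more careful. It says that "these introduced species primarily serve as a proof-of-principle to demonstrate detectability in blood" and looks to stool profiling and correlation with stool for the link to the gut.

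**The concern.** The primary endpoint measures organisms that participants are given to eat. If their DNA rises in blood, at least two explanations fit:

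- **Gut origin.** Bacteria in the intestine release DNA that reaches the circulation, so blood carries information on the gut community.
- **Food origin.** DNA contained in the yogurt or other dairy is absorbed, whether or not the gut community is represented in blood.

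The Introduction says that the route by which microbial DNA enters blood is unclear, so the second explanation is open on the article's own terms. What is at stake is the conclusion. A positive primary result could be reported as validating blood as a picture of the gut microbiome, when the endpoint supports only the narrower statement that DNA of eaten bacteria can be found in blood.

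**Working it through.** The article attaches no figure to this inference, so there is none to reproduce. The check has two parts.

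**1. Does any design feature separate the two origins?**

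| Feature | Where | What it addresses | Separates food DNA from gut DNA? |
|---|---|---|---|
| Yogurt DNA spiked into blood | 2.8.1, Fig. 3A | Analytical detection | No |
| Microbial community DNA standard | 2.8.1 | Accuracy of the pipeline | No |
| Placenta, virus-positive, organoid, pig and rat references | Fig. 3B | Background and misclassification | No |
| MRS agar counts of the yogurt | 2.7.3 | Intake of viable bacteria | No |
| Ten-day withdrawal | 2.1 | Removes both sources together | No |
| Stool YDB | 2.8.4 | Presence in stool | No: eaten bacteria and their DNA also pass into stool |
| Comparator food | 2.1 | Single arm, none | Not available |
| Sampling well after intake ends | 2.7.4 | None after day 18 | Not available |
| Fasting blood | 2.8.1 | Time since the last meal | Only in part, see below |

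A correlation between blood YDB and stool YDB does not settle the matter either. Intake is absent at D0 and present afterwards, and it can drive both measurements.

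**2. How far does fasting blood help?**

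Inputs: yogurt at breakfast (Fig. 1 legend); fasting blood (2.8.1) at morning visits 24 hours, 48 hours and 7 days after reintroduction (2.7.4); half-life of bacterial DNA in blood unknown, presumed under 24 hours by analogy with other cell-free DNA (Introduction). Assumptions of mine: first-order decay, immediate absorption, and half-lives *h* from 2 hours to the 24-hour bound.

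- Share left 24 hours after one intake: r = 0.5^(24/h).
- Level on the morning of day 18, after seven daily intakes and before any eighth, as a multiple of one intake's level: r + r² + … + r⁷.

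| Assumed h | 24 h after one intake | After seven daily intakes |
|---|---|---|
| 2 h | 0.5^12 = 0.02% | 0.02% |
| 6 h | 0.5^4 = 6.25% | 6.7% |
| 12 h | 0.5^2 = 25% | 33% |
| 24 h | 0.5^1 = 50% | 99% |

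Fasting removes directly absorbed food DNA only towards the top of this table. Slow absorption would raise every row. The article establishes neither the half-life nor the duration of absorption.

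For D0, after ten days without dairy, the same formula at h = 24 hours gives 0.5^10 = 0.1%. D0 is therefore the visit least affected by eaten dairy DNA.

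**The case against.** The strongest defence has five parts.

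- **Definition.** Section 2.5.1 treats YDB as short-stay members of the gut flora, so a change in YDB is a change in the intestinal microbiome. It also speaks of the extent of reflection, not of proof that blood mirrors resident flora. This narrows the gap between claim and endpoint, but a definition does not show whether DNA in blood came from bacteria in the gut or straight from the food.
- **The broader question is already planned.** Section 2.5.2 asks whether non-YDB DNA in blood follows shifts in the gut. This stands, and the fix builds on it. However, section 2.9 gives these taxa only a repeated measures ANOVA over time, which does not test agreement between blood and stool. Section 2.5.3 also expects non-dairy organisms to stay fairly stable, so there may be little change to follow.
- **The article is cautious elsewhere.** A reader might infer that the Abstract already declares surrogacy, or that the Discussion concedes detectability and nothing more. Neither is supported. The Abstract states a conditional aim, and the Discussion says *primarily* and adds stool correlation. The unqualified claim is in section 2.5.1.
- **Fasting samples.** They help if half-life and absorption are short, which is not established.
- **No evidence of food-DNA absorption.** Correct: the article gives no data on it. It remains an unexcluded alternative, which is enough to defeat the word *definitive* but not to predict a false result.

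**Conclusion.** The point holds as a mismatch between the claim in section 2.5.1 and what the primary endpoint can show. A positive result would show that DNA of ingested dairy bacteria is detectable in blood. It would not, by itself, be definitive on how far blood reflects the gut microbiome. The sponsor should correct this, because it changes what the trial may conclude.

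The size is qualitative. A reader might infer that, if food DNA is absorbed and gut flora are not represented in blood, the chance of wrongly declaring surrogacy equals the power of the primary test. The article does not support such a figure: it gives no effect size or standard deviation, and no rule by which p < 0.05 declares surrogacy. The decay figures above rest on assumed half-lives and first-order kinetics. They show only that fasting cannot be relied on, and the verdict does not depend on any one of them.

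**What to change.** 1. **Section 2.5.1.** Replace the claim of definitive evidence with a statement such as: a rise in blood YDB after reintroduction will show that DNA of ingested dairy bacteria is detectable in blood. This agrees with the Discussion.
2. **Section 2.5.2.** Rest any statement about blood as a surrogate on the non-YDB blood-stool comparison already named there. Leave out taxa found in the pooled yogurt DNA, which is sequenced under Fig. 3A, and other known dairy-associated taxa. The yogurt list alone is not enough: section 2.1 allows other dairy, whose bacteria may be absent from the study yogurt.
3. **Section 2.9.** Add a test that needs no change over time: is each person's blood profile closer to their own stool than to other people's? With 10 participants, each visit gives 10 own pairs and 10 × 9 = 90 pairs with others. Compare the mean dissimilarities and permute the person labels, keeping each person's visits together. Report D0 separately. Filter host reads first, and do not extract a person's blood and stool in the same batch, because either could create a false match.

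The cost is a narrower claim and one more analysis of data already collected, with no new samples, visits or participants. A close own-stool match would support representation of the gut in blood but would not prove the route, since DNA from a person's habitual non-dairy diet could also contribute.
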